### High-resolution anorectal manometry examination procedure

Bowel preparation is routinely used before the examination. The patient is placed in the left lateral position with knees and hips bent at a 90° angle, and the lubricated probe is gently inserted into the rectum. Once positioned, the probe assembly remains stationary for the duration of the study. The procedure included assessment of average resting pressure and maximum anal sphincter contraction pressure.

### Other information

Table 1 shows the information that is collected in addition to manometric findings and Wexner continence score. The study physicians will record each patient’s baseline and main examination data.

**Table 1 Tab1:** Collected information

	Baseline (T1)	After radiotherapy or chemotherapy (before surgery, T2)	After surgery (before closing the temporary stoma, T3)	Follow-up (every 3 to 6 months, T4, T5……)
Age				
Sex				
BMI				
ECOG				
Colonoscopy				
CT/PET-CT scan				
MRI scan				
TNM stage				
Defecography				
Tumor marker				

BMI, Body Mass Index; ECOG, Eastern Cooperative Oncology Group; CT, Computerized Tomography; PET, Positron Emission Tomography; MRI, Magnetic Resonance Imaging; TNM, Tumor, Node and Metastasis.

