## Introduction

### Background and rationale

Rectal cancer represents an important public health problem that compromises patients’ health-related quality of life. Worldwide in 2020, the incidence of rectal cancer was 3.8%, while its mortality rate was 3.4% [1]. Currently, total mesorectal excision (TME) is the gold standard method in sphincter-preserving therapy for locally advanced rectal cancer (LARC) [2, 3]. Neoadjuvant chemoradiotherapy (NCRT) is being used in patients with LARC (T3–T4 or N0–N1), with the purpose of reducing the local recurrence rates and increasing the likelihood of sphincter preservation [4, 5]. However, NCRT, especially neoadjuvant radiotherapy, and sphincter-saving operations are always criticized to cause a series of functional disorders, including high bowel frequency, urgency, and fecal incontinence (FI) [6–9]. These functional disorders are associated with worsening patients’ quality of life (QOL) [10, 11].

Indeed, both radiotherapy and surgery may greatly disturb anorectal function [12, 13]. However, how and to which extent the NCRT and TME on the anorectal dysfunction is still unclear. Anorectal manometry is the preferred technique to provide objective evaluation about the function of anorectal since it can identify functional sphincter weakness, poor rectal compliance, and rectal sensation impairment [14, 15]. In addition, the Wexner continence score is usually used to subjectively determine the degree of FI [16, 17]. Low anterior resection syndrome (LARS) score is another tool for the subjective evaluation of anorectal function [18, 19]. Previous studies have evaluated short-term or long-term effects of NCRT and/or surgery on the anorectal function of patients with rectal cancer through anorectal manometry, Wexner continence score and LARS score [20–22]. Particularly, prospective studies dynamically evaluating the different roles of radiotherapy, chemotherapy and surgery on anorectal function are lacking. Dynamic evaluation of the anorectal function might have implications for alleviating functional disorders and improving QOL by intervening treatments for sphincter-saving patients.

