### Allocation

The study is a prospective, observational, controlled study without randomization. Treatment decisions will be made by multidisciplinary team for eligible patients who voluntarily sign the consent form. All patients will receive evaluation of the anorectal function through anorectal manometry, Wexner continence score and LARS score before and after therapies and at follow-up visits.

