**Total Score**:	
**Interpretation: 0–20 = No LARS, 21–29 = Minor LARS, 30–42 = Major LARS**	

### Participant timeline

Recruitment started in January 2023 at The Sixth Affiliated Hospital, Sun Yat-sen University and Nanfang Hospital, Southern Medical University. The data collected from the participants and the follow-up timeline are presented in Table ​1.

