### Statistical methods

For statistical analysis of the quantitative variables with normal distribution, the mean, standard deviation (SD), median and interquartile range will be calculated. Group comparisons will be made using t tests or Mann-Whitney U test for continuous variables. Associations between the categorical variables will be tested with the Chi-Square-test or the Fisher exact test, when appropriate. Paired values (before and after therapies) will be compared for each patient using a paired t test or a Wilcoxon test. The data will be analyzed using IBM SPSS Statistics for Windows, version 27.0 (IBM Corporation, Armonk, NY, USA). A significance threshold of p < 0.05 will be adopted for all tests.

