There are some limitations in this study. The study design is observational but not randomized and blinded. At the end of the study, we will stratify the patients according to age, sex, and cancer stage. After completing the recruitment and preliminary evaluation, we will further determine whether to enlarge the sample size or not.

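### Baseline tumour distance from the anal verge is neither named as a collected variable nor in the planned stratification of a non-randomised comparison of sphincter pressure

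*Protocol article*

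**What the plan says.** **Allocation.** The Allocation section states: "The study is a prospective, observational, controlled study without randomization". It continues: "Treatment decisions will be made by multidisciplinary team for eligible patients who voluntarily sign the consent form". The factors that the team weighs are not given. The inclusion and exclusion criteria set no limit on tumour height.

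**Data.** The section Other information says: "Table 1 shows the information that is collected in addition to manometric findings and Wexner continence score". The rows of Table 1 are age, sex, BMI, ECOG, colonoscopy, CT/PET-CT, MRI, TNM stage, defecography and tumour marker. The section adds: "The study physicians will record each patient’s baseline and main examination data". Participant timeline again points to Table 1 for the data collected. Tumour distance, tumour height and anastomotic height appear nowhere in the article.

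**Analysis.** Statistical methods says: "Group comparisons will be made using t tests or Mann-Whitney U test for continuous variables". Paired tests are named for before-and-after comparisons within patients. No covariate-adjusted model is named. The limitations paragraph of the Discussion says: "At the end of the study, we will stratify the patients according to age, sex, and cancer stage".

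**Rationale for NCRT.** Background and rationale describes NCRT as used in locally advanced disease "with the purpose of reducing the local recurrence rates and increasing the likelihood of sphincter preservation".

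**The concern.** The study aims to separate the roles of NCRT, neoadjuvant chemotherapy and surgery in anorectal function. Without randomisation, that depends on handling the factors that influence both the choice of treatment and the outcome.

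Tumour distance from the anal verge is a leading candidate. If NCRT is chosen partly to make sphincter preservation possible, it will plausibly be chosen more often when the tumour is near the sphincter. A lower tumour also plausibly means surgery closer to the sphincter, and so a lower pressure afterwards whatever the neoadjuvant treatment. Both steps push in the same direction: NCRT would look worse for ARP than it is.

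Stage describes depth of invasion and spread, not distance from the sphincter, so stratifying on age, sex and stage does not deal with this. The contrast most exposed is postoperative ARP for NCRT versus surgery only. That is also the type of contrast used for the sample size, which rests on pressures at ileostomy closure.

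**Working it through.** **Is the variable named?** The Table 1 rows, the stratification sentence and the Statistical methods section were set side by side. Tumour distance is in none of them. MRI and colonoscopy are in Table 1, but as examinations, with no distance field defined.

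**How much could it matter?** The article gives no figure for this bias, so the size can only be illustrated.

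*Inputs from the Sample size section:* SDs 17 and 18 mmHg; 122 per group before loss to follow-up; design difference 45.3 − 32.7 = 12.6 mmHg. The 122 is taken as planned. The stated inputs do not reproduce it: with variance (17² + 18²)/2 = 306.5, n = 2 × (1.96 + 0.84)² × 306.5 / 12.6² gives 31 per group after rounding up. That is a separate matter and does not bear on this point.

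*Standard error of the difference in means:*

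SE = √((17² + 18²)/122) = √(613/122) = 2.24 mmHg

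*Assumptions not in the article:* 60% low tumours in the NCRT group and 30% in the surgery-only group; postoperative ARP 5 to 10 mmHg lower with a low tumour; no true NCRT effect.

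*Bias* = (difference in proportion) × (effect of a low tumour):

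- (0.60 − 0.30) × 5 = 1.5 mmHg, which is 12% of 12.6
- (0.60 − 0.30) × 10 = 3.0 mmHg, which is 24% of 12.6

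*Two-sided false-positive rate* = P(|Z + bias/SE| > 1.96):

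- bias 1.5: shift 1.5/2.24 = 0.67, rate about 10%
- bias 3.0: shift 3.0/2.24 = 1.34, rate about 27%

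**Sensitivity to the assumptions.** Suppose instead that ARP differs by 1 to 3 mmHg per cm of tumour height and that the group means differ by 1 to 3 cm (also assumed). The bias is the product of the two:

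| Bias (mmHg) | Share of 12.6 | False-positive rate |
|---|---|---|
| 1 | 8% | 7% |
| 2 | 16% | 14% |
| 3 | 24% | 27% |
| 4 | 32% | 43% |
| 6 | 48% | 76% |
| 9 | 71% | 98% |

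If the groups have the same height distribution, the bias is zero and the rate stays at 5%. The range is wide because the article fixes neither the imbalance nor the effect of height.

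**The case against.** The strongest reply is that this is a condensed article and Table 1 is not a full case report form. It has no row for treatment received, and its lead-in omits the LARS score, which is a secondary outcome. Nobody would conclude that those are not collected. This stands: the article does not show that tumour distance will go unrecorded, only that it is not named. What remains is that the article does commit to a stratification set and to group tests, and neither uses tumour distance.

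A reader might go further and infer that the confounder cannot be controlled, or that no later analysis could recover it. The article does not support that. MRI and colonoscopy are listed, and distance could be abstracted from their reports, also in retrospect.

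A reader might also count the absence of anastomotic height from the stratification as a defect. It is not. Anastomotic height is fixed at surgery, after neoadjuvant treatment, and may lie on the path from treatment to outcome. Stratifying on it could remove part of the effect under study.

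The link between low tumours and NCRT is not stated either. The Background gives reduced local recurrence as the other purpose of NCRT and ties its use to T and N category. Stage is in the stratification set. Selection on height is plausible, but it remains an inference.

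Finally, ARP is measured at baseline and again before surgery, and paired tests are planned. Changes from baseline remove stable differences in pressure between patients, and surgery cannot affect the preoperative change. This gives partial protection. It does not cover height-dependent surgical injury when groups are compared after the operation.

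**Conclusion.** The point holds in a limited form. As written, the plan leaves baseline tumour distance out of the comparison of non-randomised groups: it is not named as a collected variable, it is not in the stratification set, and the group tests are unadjusted. A lower postoperative ARP after NCRT could then partly reflect lower tumours.

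The size is unknown. A false-positive rate of about 10–27% instead of 5% follows from the assumed 60%/30% split and the assumed 5 to 10 mmHg effect; other assumed values give 7% to 98%. These figures show that a bias well below the 12.6 mmHg design difference would matter at 122 per group. They are not estimates for this study. The direction, against NCRT, rests on the inference that NCRT patients have lower tumours.

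The omission can be repaired, and the change is worth making because it replaces an unadjusted analysis with a better one at little cost.

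**What to change.** 1. Name baseline distance of the lower tumour edge from the anal verge as a collected, continuous variable. Take it from the baseline MRI or colonoscopy report, state which source takes precedence, and back-fill patients enrolled since January 2023.
2. Add it to age, sex and cancer stage in the stratification set, and tabulate it by treatment group so that any imbalance is visible.
3. Replace the unadjusted t test for between-group ARP with a regression such as ANCOVA, adjusted for baseline ARP, age, sex, stage and tumour distance. Statistical methods names no adjusted model at present, so this has to be written in.
4. Record anastomotic height for descriptive or secondary analysis only, and keep it out of the main model because it can follow from treatment.

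The cost is a small amount of data abstraction from existing reports, with no new procedure for patients. Adjustment will not remove confounding by factors that stay unmeasured. If the groups hardly overlap in tumour distance, the adjusted difference will lean on extrapolation and should be reported as such.

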### Recruitment

Patients aged 18–75 years who have been diagnosed with LARC and consider sphincter-preserving therapies are eligible for the study. After obtaining informed consent, the patient will be recruited to the study.

### Allocation

The study is a prospective, observational, controlled study without randomization. Treatment decisions will be made by multidisciplinary team for eligible patients who voluntarily sign the consent form. All patients will receive evaluation of the anorectal function through anorectal manometry, Wexner continence score and LARS score before and after therapies and at follow-up visits.

### Questionnaire used in the study

The questionnaire we use are Wexner continence score (Table 2) and LARS score (Table 3), which will be writing in Chinese thus patients can use their native language.

**Table 2 Tab2:** Wexner continence score

Type of Incontinence	Frequency				
	Never	Rarely	Some- times	Usually	Always
Solid	0	1	2	3	4
Liquid	0	1	2	3	4
Gas	0	1	2	3	4
Wears pad	0	1	2	3	4
Lifestyle alteration	0	1	2	3	4

0 = normal, 1–8 = minor incontinence, 9–14 = average incontinence, 15–20 = complete incontinence.

Never = 0 (never).

Rarely = < l/month

Sometimes = < l/week,_>l/month

Usually = < l/day, _>l/week

Always = _>l/day

**Table 3 Tab3:** Low anterior resection syndrome (LARS) score

The aim of this questionnaire is to assess your bowel function. Please tick only one box for each question. It may be difficult to select only one answer, as we know that for some patients symptoms vary from day to day. We would kindly ask you to choose one answer which best describes your daily life. If you have recently had an infection affecting your bowel function, please do not take this into account and focus on answering questions to reflect your usual daily bowel function.	
**Do you ever have occasions when you cannot control your flatus (wind)?**	
□ No, never □ Yes, less than once per week □ Yes, at least once per week	0 4 7
**Do you ever have any accidental leakage of liquid stool?**	
□ No, never □ Yes, less than once per week □ Yes, at least once per week	0 3 3
**How often do you open your bowels?**	
□ More than 7 times per day (24 h) □ 4–7 times per day (24 h) □ 1–3 times per day (24 h) □ Less than once per day (24 h)	4 2 0 5
**Do you ever have to open your bowels again within one hour of the last bowel opening?**	
□ No, never □ Yes, less than once per week □ Yes, at least once per week	0 9 11
**Do you ever have such a strong urge to open your bowels that you have to rush to the toilet?**	
□ No, never □ Yes, less than once per week □ Yes, at least once per week	0 11 16
**Total Score**:	
**Interpretation: 0–20 = No LARS, 21–29 = Minor LARS, 30–42 = Major LARS**	

### Participant timeline

Recruitment started in January 2023 at The Sixth Affiliated Hospital, Sun Yat-sen University and Nanfang Hospital, Southern Medical University. The data collected from the participants and the follow-up timeline are presented in Table ​1.

### Sample size

The sample size calculation was performed considering the results of a previous case-control study with rectal cancer patients undergoing chemoradiotherapy and/or surgery [25]. In this study, RP was significantly lower in the chemoradiotherapy group than in the surgery group (32.7 +/- 17 vs. 45.3 +/- 18 mmHg; P = 0.03) at the time of ileostomy closure. These values were introduced at PASS v11 software (NCSS, LLC. Kaysville, Utah, USA) with a power of 80%, alpha 0.05, and an enrollment ratio of 1/1, resulting in an estimated sample size of 122 participants in each group. Then, considering the need of lost to follow-up, which is estimated at around 10.0% of the cases, a total of 134 patients in each group will be required in this study.

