## Abstract

**Background:**

Neoadjuvant chemoradiotherapy (NCRT) and total mesorectal excision are standard treatment regimen for patients with locally advanced rectal cancer (LARC). This sphincter-saving treatment strategy may be accompanied by a series of anorectal functional disorders. Yet, prospective studies that dynamically evaluating the respective roles of radiotherapy, chemotherapy and surgery on anorectal function are lacking.

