### Objectives

This prospective, observational, controlled, multicentre study aims to dynamically evaluate the different roles of NCRT with surgery, neoadjuvant chemotherapy (NCT) with surgery and surgery only on the anorectal function of patients with LARC by using anorectal manometry, Wexner continence score and LARS score. In addition, the correlation between manometric findings and Wexner continence score or LARS score after different treatment regimens would be investigated.

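### The printed inputs give about 32 per group, not 122; the 80% power fits an unstated 6.3 mmHg difference and is not tied to the two contrasts with the NCT group that would separate radiotherapy from chemotherapy

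*Protocol article*

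**What the plan says.** The Sample size section takes its assumption from one previous case-control study: "RP was significantly lower in the chemoradiotherapy group than in the surgery group (32.7 +/- 17 vs. 45.3 +/- 18 mmHg; P = 0.03", measured when the ileostomy was closed. These values were entered "with a power of 80%, alpha 0.05, and an enrollment ratio of 1/1", "resulting in an estimated sample size of 122 participants in each group". After an allowance of about 10% for loss, "a total of 134 patients in each group will be required in this study". The Abstract gives a total of 402, which is 3 × 134, so the per-group number is applied to NCRT plus surgery, NCT plus surgery, and surgery only.

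The Objectives section states the aim: to "dynamically evaluate the different roles of NCRT with surgery, neoadjuvant chemotherapy (NCT) with surgery and surgery only on the anorectal function". The Abstract describes the gap to be filled: "prospective studies that dynamically evaluating the respective roles of radiotherapy, chemotherapy and surgery on anorectal function are lacking". Under Statistical methods, groups are compared with two-sample tests, each at p < 0.05. The limitations paragraph of the Discussion leaves a later enlargement of the sample open, without a rule.

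**The concern.** There are two linked problems.

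- **The stated number does not follow from the stated inputs.** A standardised difference of about 0.72 (12.6/17.5) at 80% power does not need 122 per group. A reader therefore cannot tell which difference the 80% refers to.
- **The only named contrast cannot separate the treatments.** Under Interventions, radiotherapy is given during the chemotherapy cycles, so NCRT versus surgery carries the effects of both. Radiotherapy is isolated by NCRT versus NCT, and chemotherapy by NCT versus surgery only. Neither contrast, and no NCT mean, appears in the calculation.

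At stake is how the results are read. Anyone who takes the printed 80% to cover every pairwise comparison may give a non-significant NCT contrast more weight than it can bear. The same uncertainty would carry into any later decision to enlarge the sample.

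**Working it through.** **Inputs (Sample size section).** Means 32.7 and 45.3 mmHg; SDs 17 and 18; power 80%; alpha 0.05; ratio 1:1. The article does not state sidedness; two-sided is assumed.

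Difference = 45.3 − 32.7 = 12.6 mmHg. Common SD = √((17² + 18²)/2) = √306.5 = 17.51.

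**Step 1: reproduce 122.** n per group = 2(1.960 + 0.842)² × SD² / d².

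- d = 12.6: 2 × 7.849 × 306.5 / 158.76 = 30.3, so 31 (exact t: 32).
- d = 6.3: 2 × 7.849 × 306.5 / 39.69 = 121.2, so 122 (exact t: 123).

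Other settings for 12.6 mmHg do not reach 122. One-sided gives 24–25; 90% power 41–42; 95% power 51–52; 99% power 71–72; alpha/3 at 80% power 41–42; a Mann-Whitney correction 34–38. Even alpha 0.01 with 99% power and SD 18 gives only 99–100. The stated figure is reproduced only with half the stated difference.

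**Step 2: what 122 per group delivers.** Standard error = 17.51 × √(2/122) = 2.24 mmHg. The difference detectable with 80% power is 2.802 × 2.24 = 6.28 mmHg (about 6.30 by exact t). For 12.6 mmHg, 12.6/2.24 − 1.96 = 3.66, which is a power of 99.99%.

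**Step 3: the contrasts that answer the aim.** By identity, (NCT − NCRT) + (surgery − NCT) = surgery − NCRT = 12.6 mmHg. If the NCT mean lies between 32.7 and 45.3, both terms are non-negative and the smaller is at most 6.3 mmHg. With 122 evaluable per group, SD 17.5 assumed for NCT as well, and two-sided 0.05 per contrast (exact t):

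| Assumed split | Smaller contrast | Power | Larger contrast | Power | Both significant |
|---|---|---|---|---|---|
| 50/50 | 6.3 mmHg | 79.9% | 6.3 mmHg | 79.9% | 61% |
| 67/33 | 4.2 mmHg | 46% | 8.4 mmHg | 96% | 43% |
| 75/25 | 3.15 mmHg | 29% | 9.45 mmHg | 99% | 28% |

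The last column allows for the NCT group being shared by the two contrasts. The splits are illustrations; the document gives none.

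**Step 4: sensitivity of the even-split figure.** SD 17, 17.5 or 18 gives 82.2%, 80.0% or 77.7%. With 10% lost from 134 (120–121 evaluable) it is 79.3–79.6%. With all 134 evaluable it is 83.5%, and both contrasts exceed 80% only when each lies between about 6.0 and 6.6 mmHg.

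**The case against.** It can be argued that 122 per group is about four times what NCRT versus surgery needs, and that it fits 6.3 mmHg, the even-split NCT contrast. On that view the NCT contrasts are sized after all. The number is indeed generous for the named contrast. But the text mentions neither 6.3 mmHg nor an NCT contrast, so a deliberate choice cannot be read out of it.

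Other points stand and limit what can be claimed:

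- A reader might infer that the design cannot give both NCT contrasts more than 80% power whatever the truth. The documents do not support that. The ceiling depends on NCT lying between the other groups, and no NCT value is given. With NCT at 25 mmHg, for example, the powers would be 93% and over 99.9%.
- A reader might infer that the study is too small. That does not follow either, because the uneven splits are assumptions. If chemotherapy truly has no effect, a non-significant NCT-versus-surgery result is correct, and NCRT versus NCT carries the full 12.6 mmHg at over 99.9% power.
- The article does not say that p ≥ 0.05 will be taken as absence of an effect. That is a risk of interpretation, not a stated rule.
- Paired comparisons from T1 to T2 offer a second route. In the NCT group the change before surgery reflects chemotherapy. With an assumed within-patient correlation of 0.5 to 0.7, 122 patients give 75–92% power for 4.2 mmHg (60% at 0.3). This has no concurrent control, and it does not repair the printed calculation.

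**Conclusion.** The point holds as a correction to the Sample size section. The stated inputs give about 32 per group, not 122. At 122 the named contrast has over 99.9% power, and the printed 80% corresponds to a difference of about 6.3 mmHg that appears nowhere in the text. That part rests only on the article's own figures and a two-sided 0.05 test.

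The second part is conditional. If the NCT mean lies between the other two and its SD is similar, the smaller NCT contrast has at most about 80% power at 122 evaluable per group, and reaches that only at an even split. The 46% and 29% figures show how fast power falls under assumed uneven splits; they are not predictions. Nothing here shows that the sample size itself must change.

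**What to change.** Keep N and revise the text:

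1. In Sample size, state the difference that 122 evaluable per group detects with 80% power: about 6.3 mmHg at SD 17.5, two-sided 0.05. If another input produced 122, state that input and its basis.
2. Say that 32.7 versus 45.3 mmHg describes NCRT versus surgery only, for which power is over 99%.
3. Name NCRT versus NCT and NCT versus surgery only as the contrasts that answer the objective, and show their power over a range of assumed differences (for example 6.3, 4.2 and 3.15 mmHg: 80%, 46% and 29%).
4. In Statistical methods, report each contrast as an estimate with a 95% confidence interval, and do not read p ≥ 0.05 alone as no effect. Do not use 6.3 mmHg as a margin for ruling out an effect unless it is justified clinically.

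The cost is wording in two sections, with no extra patients or procedures. The downside is that the stated power becomes less favourable for the NCT contrasts. A side benefit is that any later decision on enlarging the sample would have a named contrast to refer to.

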**Patients/design:**

The study is a prospective, observational, controlled, multicentre study. After screening for eligibility and obtaining informed consent, a total of 402 LARC patients undergoing NCRT followed by surgery, or neoadjuvant chemotherapy followed by surgery, or surgery only would be included in the trial. The primary outcome measure is the average resting pressure of anal sphincter. The secondary outcome measures are maximum anal sphincter contraction pressure, Wexner continence score and low anterior resection syndrome (LARS) score. Evaluations will be carried out at the following stages: baseline (T1), after radiotherapy or chemotherapy (before surgery, T2), after surgery (before closing the temporary stoma, T3), and at follow-up visits (every 3 to 6 months, T4, T5……). Follow-up for each patient will be at least 2 years.

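### The printed sample-size inputs give about 32 patients per group, not the stated 122, so the stated n, power and target effect are incompatible

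*Protocol article*

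**What the plan says.** The Sample size section of the protocol article bases the calculation on an earlier case-control study in which resting pressure was lower after chemoradiotherapy than after surgery alone: "32.7 +/- 17 vs. 45.3 +/- 18 mmHg; P = 0.03) at the time of ileostomy closure". It continues "These values were introduced at PASS v11 software" "with a power of 80%, alpha 0.05, and an enrollment ratio of 1/1", "resulting in an estimated sample size of 122 participants in each group". A 10% allowance for loss to follow-up raises this to 134 per group. The Abstract carries the number forward as "a total of 402 LARC patients undergoing NCRT followed by surgery", neoadjuvant chemotherapy followed by surgery, or surgery only, which is 3 × 134.

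The section gives no other difference, margin, SD, multiplicity adjustment or design effect. Under Statistical methods the planned analysis is a simple two-group test ("Group comparisons will be made using t tests or Mann-Whitney U test for continuous variables") at an unadjusted threshold ("A significance threshold of p < 0.05 will be adopted for all tests").

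**The concern.** The paragraph presents a closed calculation: it names the inputs and says they produced the result. A difference of 12.6 mmHg against SDs of 17 and 18 is a fairly large effect, and 122 per group is far more than such an effect needs at 80% power.

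The 122 is the root of both 134 and 402, so the headline size of the study rests on it. A reader who accepts the paragraph will believe the study has 80% power against 12.6 mmHg on the primary outcome, when its 80% point is about half that. This affects how both a null result and a small but significant result are read. The Discussion also says the investigators will decide, after recruitment and a preliminary evaluation, whether to enlarge the sample. That decision needs a correct statement of what the present size can detect. Finally, the calculation covers one contrast, chemoradiotherapy versus surgery, yet sets the size of all three groups.

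**Working it through.** **Inputs (Sample size section).** Means 32.7 and 45.3 mmHg; SDs 17 and 18; power 80%; alpha 0.05; ratio 1:1. Sidedness is not stated, so two-sided is assumed here and one-sided is tried below.

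**Are the inputs garbled?** With these means and SDs, a two-sample t test gives P = 0.033 at 19 per group and P = 0.029 at 20. The quoted P = 0.03 therefore fits a small study of about 20 per arm, if its arms were of equal size. The printed means and SDs are consistent with their own P value.

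**Effect size.**
- Difference: 45.3 − 32.7 = 12.6 mmHg
- Pooled SD: √((17² + 18²)/2) = √306.5 = 17.51
- d = 12.6/17.51 = 0.72

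**Required n per group.**
- Normal approximation: n = 2(1.960 + 0.842)² × SD²/difference² = 2 × 7.849 × 306.5/158.76 = 30.3, so 31
- t test (noncentral t): 31.3, so 32 (power 79.6% at 31 and 80.9% at 32)
- After 10% loss: 32/0.9 = 35.6, so 36; three groups, 108

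The stated 122 is not reproduced: 122/32 = 3.8.

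**Variants tried, n per group, otherwise with the stated inputs.**

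| Variant | n |
|---|---|
| One-sided 0.05 | 24 (normal), 25 (t) |
| SD 17 only / SD 18 only | 30 / 34 |
| Mann-Whitney (32 divided by efficiency 0.955 to 0.864) | 34 to 37 |
| Alpha 0.05/3 for three pairs | 41 (normal), 42 (t) |
| Power 90% | 41 (normal), 42 (t) |
| Power 99% | 71 (normal), 72 (t) |
| Three-group ANOVA, third mean assumed midway or equal to surgery | 39 or 29 |

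Reading 122 as a two-group total would mean 61 per group against 32, and the text says the figure is per group.

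**What would give 122.**
- Difference halved to 6.3 mmHg, SD 17.51: normal 121.2, so 122; t test 122.2, so 123
- SDs added (17 + 18 = 35), difference 12.6: normal 121.1, so 122; t test 122.1, so 123

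Either change gives d = 0.36. The match is whole-number under the normal formula and within one patient under the t test. Changing power and alpha together can also reach 122 (99% power at two-sided alpha 0.001, normal formula), but that contradicts the stated 80% and 0.05. None of these inputs is stated in the document.

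**What 122 per group delivers with the stated SDs (t test).**
- Power at 12.6 mmHg: 99.99%; at alpha 0.05/3, 99.93%
- Difference detectable with 80% power: 6.3 mmHg (d = 0.36)
- Smallest observed difference reaching p < 0.05: 1.970 × 17.51 × √(2/122) = 4.4 mmHg, compared with 1.999 × 17.51 × √(2/32) = 8.7 mmHg at 32 per group

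**Loss to follow-up.** 122 × 1.1 = 134.2, which is the plan's 134. To keep 122 after 10% loss one divides: 122/0.9 = 135.6, so 136. With 134 enrolled, 134 × 0.9 = 120.6, about 121 evaluable.

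**The case against.** The strongest counter-argument is that the error is harmless in direction. The primary comparison has ample power for 12.6 mmHg. The study is observational, with treatment chosen by a multidisciplinary team, so the larger number changes nobody's treatment. A reader who believes the paragraph understates the power, so a null result would be stronger evidence against 12.6 mmHg than that reader supposes. All of this stands and limits the harm, but it does not make the paragraph correct.

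Second, the cause is unknown. If the SDs were added by mistake, 12.6 mmHg was still the intended target and the fault lies in the SD entry. This also stands. What is certain is the mismatch on the standardized scale (0.36 against 0.72); calling 6.3 mmHg the intended difference would be a guess.

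Third, deriving 6.3 mmHg from n = 122 and then justifying it would be a rationale made up after recruitment began in January 2023. That is a fair warning about the remedy, and it is why the software entry should be looked up first.

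Fourth, the Discussion treats the size as open to enlargement. That shows the figure is provisional but does not explain it.

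Condensation in a journal article is no defence here. Nothing needs to be supplied from elsewhere: the inputs and the result are both printed, and they disagree.

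**Conclusion.** The concern holds. From the printed inputs the requirement is 32 per group (31 by the normal approximation), against a stated 122. After 10% loss it is 36 against 134, and in total 108 against 402. With 122 per group and the stated SDs the study has 99.99% power at 12.6 mmHg and 80% power at about 6.3 mmHg.

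This rests on a two-sided 0.05 comparison of two independent means with the stated SDs. The conclusion is not sensitive to those choices: each variant in the table, changed singly, stays at 72 or below.

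The discrepancy leads to too many patients for the stated effect, not too few. It must still be fixed, because the headline sample size, the stated power and the stated effect contradict one another on the primary outcome.

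**What to change.** First, retrieve the PASS entry and report what was entered. Then correct the paragraph in one of two ways, according to what the entry shows:

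- **If a smaller effect was intended:** state that 122 evaluable patients per group give 80% power at two-sided alpha 0.05 to detect about 6.3 mmHg (d = 0.36, SD 17.5) in each pairwise contrast, and justify that difference. If the three contrasts are to share the alpha, the detectable difference at 0.05/3 is 7.3 mmHg (d = 0.42).
- **If 12.6 mmHg was intended:** state 32 evaluable per group, and give the actual reason for enrolling more. Adjustment for confounding or the contrasts with the chemotherapy group would be legitimate reasons, but the text gives neither at present.

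In both cases, state the sidedness and say that the input data cover only chemoradiotherapy versus surgery. Inflate for loss by dividing by 0.9: 122 becomes 136 per group and 408 in total. Alternatively keep 134 and say that about 121 per group are expected to be evaluable.

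Cost: a reworded paragraph and a protocol or registry note. If 402 is kept, no patients are added.
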